### 2.1. Study Design

We intend to perform a two-group, non-blinded, cluster randomized, and pragmatic clinical trial with the recruitment of 380 subjects (190 per arm). The duration of the intervention will be 90 days, with data collection of outcomes performed over a one (1)-year period. 

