## 5. Statistical and Analytical Plans

We will implement an intention-to-treat (ITT) analysis, meaning all subjects randomized to either the intervention or control groups will be analyzed. Subjects who withdraw or are lost to follow-up will have their data analyzed up to their last recorded home nursing visit.

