### 5.1. Outcome Measures

Dichotomous Outcomes: The frequency of outcomes will be determined, and we will utilize time-to-event analyses. The hazard ratios (HRs) along with their 95% confidence intervals (CIs) will be determined using a stratified Cox proportional hazards model.Continuous Outcomes: The differences between the intervention and control groups, along with their 95% CIs and corresponding *p*-values, will be documented.

Both patient-level and cluster-level data will be analyzed. We will address any imbalances in individual data by adjusting statistically using a mixed-effects Cox regression model performed by a statistician blinded to the group allocation. 

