## Figures and Tables

**Table 1 nutrients-16-00299-t001:** Exclusion criteria for the INCA Trial.

	Exclusion Criteria
1.	Septicaemia.
2.	Poorly controlled diabetes (*glycated hemoglobin level > 8.5%)* [20,26].
3.	Consumption of supplements will lead to fluid intake in excess of fluid restriction for the following conditions: Advanced renal disease not on dialysis (KDIGO [21,22] Stage G4 with an eGFR of 15–29 mL/min/1.73 m^2^ and Stage G5 with an eGFR of less than 15 mL/min/1.73 m^2^); Heart failure with reduced ejection fraction [27]; Advanced decompensated alcoholic and non-alcoholic liver cirrhosis [28,29].
4.	Current neoplastic disease or last chemotherapy or radiotherapy less than one year ago.
5.	Currently on immunosuppressive therapy.
6.	Palliative with *a lifespan of ≤ 3 months.*
7.	Known allergy reaction to L-arginine or phenylketonuria.
8.	Presence of an infected wound *(if it is the only pressure injury present on the participant).*
9.	Untreated diagnosed osteomyelitis [18,19,30,31,32].
10.	Pregnant women and children (there is limited evidence on the use of arginine in these groups).

**Table 2 nutrients-16-00299-t002:** Outcomes and the methods of measurement to be used in the cluster RCT.

Type	Outcome	Outcome Description	Measurement Method	Data Collection Time Point (t) and Time Frame	Performed by
Primary	Wound	Change in the area of pressure injury (cm^2^) from the baseline	Assessed by the change in wound area ^#^ from the baseline to the follow-up time points and measured with a 3D wound imaging device at the time of follow-up.	t_0_ baseline, t_1_ 30 days, t_1_ 60 days, t_3_ 90 days, t_4_ 6 months, and t_x_ 1 year Time frame: 1 year	Nurse
		The proportion of participants with ≥40% area reduction	Assessed by the number of participants with wound area ^#^ reduction ≥ 40% at the time of follow-up versus the baseline.	t_1_ 30 days, t_1_ 60 days, t_3_ 90 days, t_4_ 6 months, and t_x_ 1 year Time frame: 1 year	Nurse, CRC
Secondary	Wound	The proportion of participants with complete wound healing of the main wound	Assessed by the number of participants with complete healing of a wound ^#^, determined by clinical assessment and pressure injury staging.	t_1_ 30 days, t_1_ 60 days, t_3_ 90, t_4_ 6 months days, and t_x_ 1 year Time frame: 1 year	Nurse, CRC

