	Clinical	Mortality	Assessed by the occurrence and time-to-event of all-cause mortality during the study period.	t_1_ 30 days, t_1_ 60 days, t_3_ 90 days, and t_x_ 1 year Time frame: 1 year	Nurse, CRC
		Unplanned hospital admissions	Assessed by the occurrence and time-to-event of one or more unplanned hospital admissions during the study period.	t_1_ 30 days, t_1_ 60 days, t_3_ 90 days, and t_x_ 1 year Time frame: 1 year	Nurse, CRC
Others	Pre-specified Outcome	Adherence to nutrition Supplementation intake	Assessed by the number of participants with >75% consumption of oral nutritional supplements and Arginaid, where the servings of products consumed are counted with confirmation of intake during follow-up.	t_1_ 30 days, t_1_ 60 days, and t_3_ 90 days Time frame: 1 year	Dietitian, Nurse, CRC
		Wound depth	Measured (millimeters) using sterile forceps and rulers at follow-up.	t_0_ baseline, t_1_ 30 days, t_1_ 60 days, 90 t_3_ days, and t_x_ 1 year Time frame: 1 year	Nurse
		Hospital length of stay	Assessed by the number of days for each unplanned hospital admission.	If available: t_x_ 1 year Time frame: 1 year	Nurse, CRC
		Wound duration and time-to-heal	Measured by days to complete healing for participants with complete wound healing. Additional interaction of time with intervention and other covariates will be included and tested	t_x_ 1 year Time frame: 1 year	Investigators
		Frequency of unplanned hospital admissions	Assessed by the frequency of occurrence per participant and the sum of unplanned hospital admissions of all participants.	t_x_ 1 year	Investigators

^#^ The data from the measurement of the pressure injury with the highest severity will be used in the analysis for the primary endpoint. If the wound of the highest severity is deemed unmeasurable (e.g., too small of a surface area), we will select the wound with the next highest severity. CRC: clinical research coordinator; HRQOL: health-related quality of life; PI: pressure injury.

**Table 3 nutrients-16-00299-t003:** Study schedule of enrolment, interventions, and assessments.

	STUDY PERIOD							
	Enrollment	Allocation	Post-Allocation					Close-Out
TIMEPOINT	*−7 to −1d* −*t_0_*	Baseline *t_0_*	*30d t_1_*	*60d t_2_*	*90d t_3_*	*6m t_4_*		*1y* *t_x_*

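### Table 2 defines time-to-heal only for participants who healed, so any between-arm comparison on that row can hide or reverse a healing benefit

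*Protocol article*

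**What the plan says.** The row on wound duration and time-to-heal in Table 2 (Figures and Tables) sits in the last tier, Others, as a pre-specified outcome with a one-year time frame. Its measurement entry reads "Measured by days to complete healing for participants with complete wound healing", followed by "Additional interaction of time with intervention and other covariates will be included and tested". It does not say what happens to participants who stay unhealed, die or withdraw.

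Three other places bear on it:

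- Section 5 sets an intention-to-treat analysis in which "all subjects randomized to either the intervention or control groups will be analyzed". It adds: "Subjects who withdraw or are lost to follow-up will have their data analyzed up to their last recorded home nursing visit".
- Section 5.1 says of dichotomous outcomes: "The frequency of outcomes will be determined, and we will utilize time-to-event analyses". Hazard ratios are to be "determined using a stratified Cox proportional hazards model".
- Table 2 has a separate secondary outcome, "The proportion of participants with complete wound healing of the main wound". Its mortality and unplanned-admission rows are defined by whether and when the event occurs, with no restriction to participants who had it.

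**The concern.** Whether a wound heals within the year is something the care bundle is meant to change. Restricting the time variable to healed wounds therefore selects participants on a post-randomisation result, and the healers in the two arms need not be alike. Two distortions follow. Slow control wounds that never close contribute no time, so a true acceleration looks smaller than it is. And if the bundle closes some hard wounds late, those late times raise the intervention arm's average, so the arm that healed more wounds can look slower.

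At stake is the reading of this one outcome. A difference in days to healing is easy to quote as a treatment effect, and on this definition neither its sign nor its size could be read that way.

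**Working it through.** **Nothing to reproduce.** The documents give no healing rate, median, hazard ratio or power for time-to-heal. Every healing rate below is an assumption. From the documents come the one-year horizon (section 2.1, taken as T = 365 days), 190 per arm, and 20% mortality plus 10% withdrawal (section 2.4).

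**Step 1: constant healing rates.** If a proportion p of controls heals by T, the daily rate is λ = −ln(1 − p)/T. With S = exp(−λT):

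- mean time among healers = 1/λ − T·S/(1 − S)
- restricted mean time with an open wound, all participants = (1 − S)/λ

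For p = 0.40 in controls: 1/λ = 714.5 and 365 × 0.60/0.40 = 547.5, so the healers-only mean is 167.0 days. Doubling the rate gives 1/λ = 357.3 and S = 0.36. Then 365 × 0.36/0.64 = 205.3, and the mean is 152.0 days.

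True rate ratio 2, control versus intervention:

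| Healed by 1 year | Healers-only mean (days) | Gap | All-participant restricted mean (days) | Gap |
|---|---|---|---|---|
| 20% vs 36% | 175.7 vs 169.0 | 6.7 | 327.1 vs 294.4 | 32.7 |
| 40% vs 64% | 167.0 vs 152.0 | 15.0 | 285.8 vs 228.6 | 57.2 |
| 60% vs 84% | 155.0 vs 129.6 | 25.4 | 239.0 vs 167.3 | 71.7 |

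At a rate ratio of 1.5 and 40% control healing, the healers-only means are 167.0 and 159.4 days, a gap of 7.6. The attenuation is milder when most wounds heal.

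**Step 2: extra slow wounds heal.** Suppose 30 of 100 controls heal at a mean of 75 days. The intervention heals the same 30 at the same times, plus k further wounds at a mean of 240 days. The healers-only mean is (30 × 75 + k × 240)/(30 + k). For k = 5, 10, 15 and 20 this is 98.6, 116.2, 130.0 and 141.0 days, against 75 in control. Nobody healed later, yet the intervention looks slower.

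**Step 3: simulation.** 190 per arm, 30% attrition over the year, 1,000 runs; clustering and the spacing of visits ignored. A Welch test among healers was compared with a Cox model in everyone.

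- *Slow wounds helped.* In both arms 40% of wounds heal at a mean of 75 days. The rest heal at a mean of 1,500 days in control and at three times that rate under intervention. Observed healing is 48% vs 64%. The Cox model (hazard ratio about 1.49) finds a significant benefit in 82% of runs. Healers-only means are 90 (control) vs 102 days, with significant benefit in 0.3% of runs and significant apparent harm in 19%.
- *Uniform rate ratio 1.6.* Observed healing is 34% vs 48%. The Cox model finds benefit in 83% of runs. Healers-only means are 157 vs 147 days, with significant benefit in 6.5%.

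**The case against.** The strongest reply is that the sentence stands in a measurement column. Days to healing exist only for wounds that heal, and the article nowhere says that mean days among healers will be compared between arms. The planned interaction could be a time-varying effect in a Cox model. This stands in part: the wording is ambiguous, and the healers-only mean contrast calculated above is one way of following it. But the row names its population and then promises a test involving intervention. The mortality and admission rows in the same table carry no such restriction. Where the article excludes participants elsewhere (section 5.4), it labels the analysis per-protocol; this row has no label.

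A reader might go further and infer that the trial's healing benefit as a whole could be hidden. The documents do not support that. Complete healing of the main wound is a separate secondary outcome, and sections 5 and 5.1 together imply a Cox analysis of it in all randomised participants. Time-to-heal is absent from sections 3.1 and 3.2, does not enter the sample size, and is not the economic outcome.

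A reader might also see a direct contradiction with section 5.1. That is too strong. Section 5.1 addresses dichotomous outcomes and never mentions censoring, which is only implied by the Cox model. The two places are inconsistent in approach, not opposed in wording.

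Finally, competing-risk detail could fairly be left to an analysis plan. The population on which an outcome is defined is different, because the article has already fixed it.

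**Conclusion.** The point holds for this row only. As defined, any between-arm comparison of time-to-heal conditions on a post-randomisation outcome, departs from the stated intention-to-treat principle, and can mask or reverse a benefit. Such distortion is possible, not certain.

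Its size cannot be fixed from the documents. Under constant rates and a true ratio of 2, the healers-only gap runs from about 7 to 25 days as assumed control healing runs from 20% to 60%. A reversal needs a particular pattern, in which the intervention mainly closes additional slow wounds. Primary, secondary and economic conclusions are unaffected. The change is worth making because the outcome is pre-specified and the correction is small.

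**What to change.** Redefine the Table 2 row as time from baseline to first documented complete healing of the index wound in all randomised participants. Censor unhealed participants at their last wound assessment, handle death as a competing event, and analyse in line with section 5.1. State that any time-by-intervention interaction is tested in that model. Days to healing among healers may be kept as a within-arm descriptive summary, with no between-arm test.

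The cost is the rewording of one row. Table 3 already schedules wound assessment and mortality at 30, 60 and 90 days, 6 months and 1 year, so no new data are needed.

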### 2.5. Randomization

We will randomize patients into two groups using a cluster randomization method, where the patient population is stratified into two groups based on the locality (postal code) and a random 1:1 block allocation of postal codes (under the care of nursing teams) to either intervention or control group. The allocation of the groups will be concealed until participation is fully confirmed. 

The primary reason for cluster randomization is to limit treatment contamination between the intervention and control groups. As the nurses from home nursing services are allocated to the care of multiple patients within the same neighborhood (based on postal code), individual randomization may increase the risk of the control group learning about the nutritional intervention (type II error) from interactions with the assigned home care nurse.

We will engage a statistician who is not associated with recruitment to generate a random number list to determine the order in which the recruiting staff will visit the specified postal codes for participant recruitment. Postal codes with low residential density in Singapore (limited cluster size) may be excluded or combined with other postal codes if feasible. 

We aim to recruit 8 to 10 subjects per week and finish recruitment in 35 to 50 weeks. We determined this rate of recruitment as there are currently 500 to 600 individuals under home nursing care with known PI(s), with the expectation that 20% to 30% of individuals will not meet the selection criteria. For patients with multiple wounds, all the PI(s) in stages II and above will be included in the analysis.

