### 3.1. Primary Outcome Measurements 

Change in Pressure Injury Area from the Baseline: Measurement of the alteration in the surface area of the identified pressure injury (PI) at identified time points;Proportion of Participants with 40% or Greater Area Reduction: Calculation of the percentage of participants who exhibit a reduction in the PI area by at least 40% at the same time points.

For participants with multiple PIs, the most severe or largest same-stage PI will be selected for primary analyses. Data from additional PIs will contribute to secondary analyses. Assessments and treatment documentation will be conducted during scheduled home nursing visits. Both objective and patient-reported outcome measures are used for the secondary outcome measurements to ensure that crucial additional information is collected from the participant’s perspective. 

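### The Table 2 footnote allows an index wound that is too small to measure to be replaced, without limiting this to baseline, so a near-healed responder could be scored on another wound

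*Protocol article*

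**What the plan says.** Three places in the protocol article bear on which wound is analysed.

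- **Section 3.1 (Primary Outcome Measurements).** For participants with several pressure injuries, "the most severe or largest same-stage PI will be selected for primary analyses". The others are kept for later: "Data from additional PIs will contribute to secondary analyses".
- **Table 2, footnote #.** "The data from the measurement of the pressure injury with the highest severity will be used in the analysis for the primary endpoint". If that wound "is deemed unmeasurable (e.g., too small of a surface area), we will select the wound with the next highest severity".
- **Section 2.5 (Randomization).** "For patients with multiple wounds, all the PI(s) in stages II and above will be included in the analysis". The section does not say which analysis.

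The marker # is attached to both primary outcomes. The responder row reads "Assessed by the number of participants with wound area ^#^ reduction ≥ 40% at the time of follow-up versus the baseline", and the row for change in area carries the marker on an area imaged at follow-up. It is also attached to two secondary outcomes, increased severity and complete healing; the latter reads "Assessed by the number of participants with complete healing of a wound ^#^, determined by clinical assessment and pressure injury staging".

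**The concern.** The only example of an unmeasurable wound in the footnote is a small one, and both primary outcomes reward wounds for becoming small. If the footnote is applied at a follow-up visit, a wound that has almost closed is a clear success on the responder outcome. It may nevertheless be replaced by a second wound that has shrunk by less than 40%. The resulting misclassification depends on the outcome itself. If the intervention works, more wounds in that arm reach the trigger, and a real effect may be diluted. Deeming a wound unmeasurable is also a judgement, and section 2.7 states that the nurses who measure wounds are not blinded.

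Separately, section 3.1 breaks ties by size but has no fallback for an unmeasurable wound, while the footnote has a fallback but no tie-break. Neither says where an unstageable wound, which section 2.2 makes eligible, ranks in severity.

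**Working it through.** **Step 1: the wording side by side.**

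| Place | How the wound is chosen | Tie-break | Fallback | When judged |
|---|---|---|---|---|
| Section 3.1 | Most severe | Largest of same stage | None | Not stated |
| Table 2 footnote | Highest severity | None | Next most severe if unmeasurable | Not stated |
| Section 2.5 | No index wound; all stage II+ wounds | n/a | n/a | n/a |

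No section fixes the index wound at baseline, and none says how a wound too small to image at follow-up is scored. There are thus two partly matching index rules and one loose statement.

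**Step 2: the plan's own figure.** Section 2.4 gives 144 per arm for an odds ratio (OR) of 2.0, 80% power and two-sided 5%, without a control rate. The figure is attainable but cannot be tied to a single control rate. The log-odds-ratio formula gives 144 at a 30% control rate, and the two-proportion formula with continuity correction gives 144 at 40%. At 50% v 66.7% (OR 2.0), the pooled formula needs 137 per arm, and 144 per arm has 82.2% power. That is the baseline used below.

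**Step 3: illustration of a swap at follow-up.** All of these inputs are assumptions:

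- response without swapping: 50% control, 66.7% intervention;
- index wound closed or too small: c = 15% control, 25% intervention;
- share with a second measurable wound: s = 40% (also 20%);
- every such wound is swapped when a second one exists;
- f = share of second wounds with less than 40% reduction.

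Responders lost in an arm = c × s × f. Power uses the pooled two-proportion formula at 144 per arm.

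*Case A: second wounds respond at 50% in both arms (f = 0.5).*

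- Control: 0.15 × 0.40 × 0.5 = 0.030, so 50.0% becomes 47.0%.
- Intervention: 0.25 × 0.40 × 0.5 = 0.050, so 66.7% becomes 61.7%.
- OR = (0.617/0.383)/(0.470/0.530) = 1.81; power 70.7%.

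*Case B: second wounds respond at their own arm's rate (f = 0.5 control, 0.333 intervention).*

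- Control: 47.0%, as in A.
- Intervention: 0.25 × 0.40 × 0.333 = 0.033, so 66.7% becomes 63.3%.
- OR = (0.633/0.367)/(0.470/0.530) = 1.95; power 79.9%.

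| Share with second wound | Case A | Case B |
|---|---|---|
| 40% | OR 1.81, power 71% | OR 1.95, power 80% |
| 20% | OR 1.90, power 77% | OR 1.97, power 81% |

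If instead 20% of wounds close in both arms, with s = 40% and f = 0.5, each arm loses 0.20 × 0.40 × 0.5 = 4.0 points, giving 46.0% v 62.7% and power 81.4%. The loss is then under one point. The harm comes mainly from unequal healing combined with second wounds that do not share the treatment effect.

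**The case against.** The strongest reply is that the footnote describes a single choice at baseline. Section 3.1 defines the primary outcome on one identified injury followed over set time points, and both passages speak of selecting a wound. Table 2 names complete healing of the main wound as an outcome and attaches the same marker to it. If the marker removed wounds as they closed, that outcome would defeat itself. Under this reading there is no bias. The reply stands to this extent: the baseline reading is reasonable and may be what was meant, but the text does not say so.

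Four stronger readings are tempting, and the documents do not support them.

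- *The index wound is defined in three conflicting ways.* Section 2.5 defines no index wound and fits with section 3.1: all wounds are analysed, the additional ones in secondary analyses.
- *Correlated wounds are pooled as if independent.* No section pools wounds for a primary outcome, and the responder outcome counts participants.
- *A healed wound is replaced by rule.* The footnote speaks of unmeasurable wounds. Healing is a separate outcome, judged clinically and by staging. The illustration treats closed and too-small wounds together, which may overstate how often the trigger is met.
- *A new wound, or another wound's area set against the original baseline, enters the primary outcome.* Nothing provides for subtracting across wounds, and a new wound has no baseline from which to measure change.

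Detailed scoring rules are often left to a full protocol or analysis plan. Here, however, the article itself states a substitution rule for the primary endpoint and leaves open when it applies.

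**Conclusion.** The point holds as a defect in a stated rule for the primary endpoint. Read literally at a follow-up visit, the footnote allows a near-healed index wound to be replaced, and nothing else in the article rules this out. It permits the swap without mandating it, and only participants with more than one wound could be affected. The mismatch between section 3.1 and the footnote is a smaller drafting fault.

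A reader might infer that the trial will lose a definite amount of power. It cannot be quantified from the article. With the assumed 40% having a second wound, power goes from 82% to 71% if second wounds respond at 50% in both arms, but only to 80% if they respond at their own arm's rate. With 20% having a second wound, the range is 77% to 81%. If the footnote is applied only at baseline, there is no loss. The case for correction is that a primary endpoint rule should not admit a reading that scores a success as a failure.

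**What to change.** Use one rule in section 2.5, section 3.1 and the Table 2 footnote:

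1. The index wound is the highest-stage measurable pressure injury at baseline, the largest if tied, with a stated place for unstageable wounds in the ranking.
2. It is fixed before the first follow-up and not changed afterwards.
3. The step to the next most severe wound applies at baseline only.
4. At follow-up, an index wound that is closed or too small to image is scored as area 0, that is, a 100% reduction.
5. Other wounds enter secondary analyses only, and section 2.5 says so.

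The cost is wording in three places and an index-wound flag in the database; participants are not affected. Recruitment has started, so this is best settled before the first interim analysis at 100 subjects (section 5.5).
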